### Study procedures and participant timeline

A SPIRIT flow diagram gives an overview of the study procedures (Table 2). After the inclusion visit, patients will be monitored twice during potentiated radiotherapy: at the beginning and at the end of radiotherapy. A visit is then planned three months after the end of radiotherapy. The other follow-up visits will be carried out every 6 months (M9, M15, M21, M27). The diagrammatic illustration of the study is presented in Fig. 2.

**Table 2 Tab2:** Spirit flow diagram

		**Potentiated radiotherapy**		**Follow-up visits**				
**Assessment**	Baseline	W1	W7	M3	M9	M15	M21	M27
**Day**	-30 à 0	0 à 7	42 à 49					
*Medical history*	x							
*Clinical examination*	x	x	x	x	x	x	x	x
*Blood sample for cDNA research*	x			x^a^				
*Cervico-thoracic scan*	x			x	x	x	x	x
*PET-CT scan*	x			x^a^				
*Histological examination of the tumor or a lymph node*	x							
*Mutation profiling by NGS on FFPE, plasma and leukocytes*	x							
*p16 immunohistochemistry on FFPE*	x							
*HR-HPV genotyping by real-time PCR on FFPE*	x							
*HR-HPV genotyping by NGS on FFPE*	x							
*Doses received, fractionation for radiotherapy*			x					
*Data on the potentiating treatment received*			x					

*W* Week, *M* Month, *FFPE* Formol fixed paraffine embedded, *PET-CT* positon-emission tomography computed-tomography, cDNA circulating DNA, PCR Polymerase chain reaction, *HR-HPV* High risk human papilloma virus

^a^*In case of residual cervical adenomegaly at cervico-thoracic scan*

**Fig. 2 Fig2:**
[figure not shown]
Scheme of the study

### Statistical analysis

#### Sample size calculations

Since the negative predictive value (NPV) of PET-CT to detect residual nodal disease in the context of our study is known to be very good (95–97%), we choose to focus on the group of patients with an indication for salvage adenectomy. The detection of ct/cvDNA should enable the identification of patients for whom this adenectomy is indeed necessary. This question means assessing the positive predictive value (PPV) of the ct/cvDNA predictor (detectable versus non-detectable) in relation to the lymph node dissection result (positive versus negative). For sample size determination, we hypothesise that the PPV of ct/cvDNA is at least 85% (the value obtained by Tanaka et al*.* being 100% from a calculation performed on 6 patients with detectable cvDNA [20]). Given an estimated 50% positive dissection rate among patients with an indication for salvage adenectomy, the inclusion of 28 patients is required to ensure a power of 80% at an alpha risk of 5% to show a PPV is greater than 50% (value taken as reference, equal to the upper limit of the imagery PPV estimate). This sample size will also enable the estimation of the NPV with a 95% confidence interval (CI) (Wilson) with a half-length equal to 16.5% (for an expected NPV of 89.7% obtained by Tanaka et al*.* [20]). To ensure the inclusion of 28 patients with adenectomy indication, n = 56 patients are required, since the proportion of patients with this indication after imagery following potentiated radiotherapy is estimated to be about 50% in our study population. Finally, assuming a low attrition rate of 10% (the time between inclusion and end of treatment being relatively short), n = 63 patients are required. Taking into account the additional risk that only 85% of the patients will have detectable ct/cvDNA [21], we estimate that it will be necessary to screen around 75 patients.

Recruitment will be complete once 32 patients with an indication for neck dissection are included and evaluable (this sample size takes into account the 10% attrition rate).

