## Background

With about 600 000 new cases per year, head and neck cancers (HNC) rank in 6^th^ position among the most common malignancies worldwide [1, 2]. More than half of the patients present a locally advanced stage at diagnosis [3]. The main risk factors for developing HNC are tobacco and alcohol consumption. High-risk papillomavirus (HPV) infection is also a cause of HNC, particularly for oropharynx cancer [4–6]. Despite treatment, 30 to 50% of patients relapse within 2 years and median survival does not then exceed one year [7–9]. The standard treatments for HNC are radiotherapy, surgery and chemotherapy [6].

Post-treatment follow-up of patients requires, among other things, a thorough clinical examination and repeated imagery investigations. The main difficulty lies in the interpretation of the results of these examinations as a result of post-operative and post-radiation changes that are difficult to distinguish from residual or recurrent tumour [10, 11].

The persistence of residual disease at the end of radiotherapy treatment is a major prognostic issue. 18F-fluorodeoxyglucose (FDG) positron emission tomography-computed tomography (PET-CT)-guided surveillance, with a negative predictive value of 95–97%, has proven to be non-inferior to cervical curage in CETEC with residual adenomegaly after radio-chemotherapy [12, 13]. Cervical curage is now indicated only if the response assessed by PET-CT is only partial. Nevertheless, the ability of PET-CT to predict residual disease is unsatisfactory because of a high frequency of false positives, due to inflammatory remodelling, with a positive predictive value of about 20–50% [14].

Currently, up to 50% of patients have residual adenomegaly after treatment, and only 30% have viable disease at the time of neck dissection [15, 16]. However, the acute and late complications to which patients who have undergone adenectomy are exposed are not negligible and can damage their quality-of-life (haemorrhage, scar disunion, alteration of swallowing function, etc.) [17–19].

Sensitive and reproducible detection of residual disease after treatment is a major issue for these patients. This is the context of our study, which aims to evaluate the prediction of residual disease using circulating DNA detection after potentiated radiotherapy for locally advanced head and neck cancer.

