## Trial status

The study was approved by the ethics committee on December 29^th^, 2022 (CPP Ouest-1). The recruitment is expected to begin in the first half of 2023. Follow-up and data collection will be complete in 2028.

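### The 50% dissection-indication rate equals the Background's ceiling for a wider group and does not fit its 30% viable-disease figure, so 75 screened is a best case

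*Protocol article*

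**What the plan says.** All places are in the protocol article.

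- Sample size calculations: 28 patients with an indication become 56, "since the proportion of patients with this indication after imagery following potentiated radiotherapy is estimated to be about 50% in our study population". A 10% attrition rate gives 63. With 85% having detectable cDNA, "we estimate that it will be necessary to screen around 75 patients". The 28 itself rests on a second 50%: "Given an estimated 50% positive dissection rate among patients with an indication for salvage adenectomy". Recruitment ends at 32 evaluable patients with an indication.
- Background: "Currently, up to 50% of patients have residual adenomegaly after treatment, and only 30% have viable disease at the time of neck dissection". It also says: "Cervical curage is now indicated only if the response assessed by PET-CT is only partial". PET-CT is given a PPV of about 20–50% and an NPV of 95–97%.
- Study procedures, footnote to Table 2: the M3 PET-CT and M3 blood sample are done "In case of residual cervical adenomegaly at cervico-thoracic scan".
- Study design and Trial status: enrolment of 36 months, a total of 30 months per patient, a start in the first half of 2023, and "Follow-up and data collection will be complete in 2028".
- Independent data monitoring committee: the sample-size assumptions and the recruitment rate are reviewed after the first 20 eligible patients.

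**The concern.** Patients with a dissection indication are a subset of those with residual adenomegaly: the scan selects for PET-CT, and PET-CT then selects for dissection. The planning rate for the subset nevertheless equals the Background's upper limit for the whole group. It can hold only if adenomegaly is at that limit and no patient with adenomegaly has a complete metabolic response. The plan itself expects PET responses to vary, since one secondary objective relates cDNA to metabolic response within this group.

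The two planning figures of 50% also imply more viable disease than the Background allows. At stake are the screening number, the enrolment period and the completion date. On one reading of the Background, the number of cDNA-positive patients on which the power rests is at stake too.

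**Working it through.** **1. The plan's own chain reproduces.** 28 / 0.50 = 56; 56 / 0.90 = 62.2, so 63; 63 / 0.85 = 74.1, so around 75. Forward: 75 × 0.85 × 0.90 × 0.50 = 28.7. The arithmetic is sound; the question is the 0.50.

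**2. What lies behind 28.** A normal-approximation one-sample test of PPV 85% against 50%, two-sided 5%, 80% power, gives 13.4, so 14 cDNA-positive patients. Doubling for the 50% rate gives 28. The stated Wilson half-length of 16.5% at NPV 89.7% also reproduces at n = 14. The plan thus takes the cDNA-positive share to equal the positive-dissection rate.

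**3. Consistency of the inputs.**
- Planning figures: 0.50 indicated × 0.50 positive = 25% of patients with viable nodal disease.
- Background: at most 0.50 adenomegaly × 0.30 viable = 15%.

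**4. Two readings of the Background's 30%.**

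*Reading A: 30% of patients with adenomegaly have viable disease.* Keeping 50% positive dissections, the indication rate is at most 0.15 / 0.50 = 30%. Allowing for missed disease in PET-negative patients, the PET-positive share of adenomegaly is (0.30 − 0.05) / (0.50 − 0.05) = 0.556 at NPV 95% and (0.30 − 0.03) / (0.50 − 0.03) = 0.574 at NPV 97%. The indication rate is then 27.8% to 28.7%.

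*Reading B: 30% of dissections are positive.* This sets no limit on the indication rate. It conflicts instead with the 50% positive-dissection rate. By the plan's own equating of the two shares, 32 patients give 32 × 0.30 = 9.6, about 10 cDNA-positive patients. Reaching 14 would need 14 / 0.30 = 46.7, so 47 indicated patients.

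**5. Yield and screening need by indication rate.** Yield = 75 × 0.85 × 0.90 × rate. Screening for 28 uses the plan's chain, rounded up at each step.

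| Indication rate | Evaluable from 75 screened | Screened for 28 |
|---|---|---|
| 50% | 28.7 | 75 |
| 40% | 23.0 | 92 |
| 35% | 20.1 | 105 |
| 30% | 17.2 | 124 |

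At 30% the chain is 28 / 0.30 = 93.3, so 94; 94 / 0.90 = 104.4, so 105; 105 / 0.85 = 123.5, so 124. For 32 at 30%: 32 / (0.30 × 0.85) = 125.5 if the 32 already covers attrition. If attrition is counted again, the steps are 107, 119 and 140.

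Reading B with a 50% indication rate reaches the same screening number for 14 cDNA-positive patients: 47 / 0.50 = 94, then 105 and 124.

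**6. Time.** The documents give no accrual rate. Assuming a constant 75 / 36 = 2.08 screened per month, 124 take about 60 months and 140 about 67. A start in the first half of 2023 plus 36 plus 30 months ends in the second half of 2028, as stated. With 60 months of enrolment it ends in the second half of 2030.

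**7. Power under Reading B.** Exact binomial, PPV 85% against 50%. With 10 cDNA-positive patients, 9 must be true positives, and power is 54% at one-sided 5% and at 2.5% per tail alike. The like-for-like figures at the planned 14 are 85% and 65%.

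**The case against.** The strongest answer has three parts.

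First, the sample size section labels its 50% as an indication rate in its own study population: node-positive, stage III to IVb, cDNA-positive. The Background is general literature, and a selected population may differ. This stands as far as it goes. A reader might infer that the adenomegaly figure was copied in under the wrong label; the document does not show that. It shows an unsourced rate equal to the ceiling of a wider group.

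Second, the Background's 30% is ambiguous. A reader might conclude that 75 screened will yield 17 evaluable patients. That needs Reading A together with 50% positive dissections; Reading B fixes no indication rate. The objection stands against a single figure of 17 but does not rescue the inputs, because on either reading one of the two planning figures of 50% fails to fit.

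Third, recruitment runs to 32 evaluable patients, and the committee checks the assumptions after 20. A reader might infer a final analysis on 17 patients with reduced power. Nothing in the document closes the trial at 75 screened, so that inference is unsupported. The stop rule does not protect the schedule, however, and under Reading B it does not protect the number of cDNA-positive patients. The committee review comes mid-trial, whereas this inconsistency is visible now.

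**Conclusion.** The point holds as an inconsistency between stated planning inputs. On the document's own figures, 50% is the most the indication rate can be, so around 75 screened is a best case. The two planning rates imply 25% viable nodal disease where the Background implies at most about 15%.

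Under Reading A the indication rate is at most about 30%. Reaching 28 evaluable patients then takes about 124 screened, and 32 takes about 125 to 140. Enrolment would last about 60 months or more if screening stays at 75 per 36 months, which is an assumption. The consequence is more screening and time, with the sample at analysis unchanged.

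Under Reading B the indication rate may stand, but 32 patients bring only about 10 cDNA-positive patients and power of about 54%, provided the cDNA-positive share follows the positive-dissection rate as the plan assumes.

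The documents do not settle which reading is meant. The primary test and the stop at 32 are not in question here.

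**What to change.** In Sample size calculations:

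1. Replace the single 50% by (rate of residual adenomegaly) × (partial PET-CT response among those patients), and give the source of each factor, including any local data.
2. State what the Background's 30% refers to, and reconcile the product with the 50% positive-dissection rate. If dissections are expected to be positive less often than 50%, restate the expected number of cDNA-positive patients and the power.
3. Give yield and screening as a range over indication rates of 30% to 50%: about 17 to 29 evaluable from 75 screened; about 75 to 124 screened for 28; about 125 to 140 for 32 at 30%. Say whether the 32 already absorbs attrition.
4. In Study design and Trial status, make the 36-month enrolment and the 2028 completion conditional on this rate.

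The cost is rewording and a less favourable screening estimate. Procedures, the primary analysis and the stop at 32 stay as they are, unless step 2 shows that 32 gives too few cDNA-positive patients.

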### Data analysis

#### Analyses of the primary endpoint

The primary analysis of the trial is the estimation of the PPV of ctDNA/cvDNA detection at 3 months post-treatment in predicting the outcome of neck dissection. The contingency table for this analysis is presented in Fig. 1. This analysis will be performed on the population undergoing neck dissection. A point estimate and CI will be provided and the PPV will be compared to the reference value of 50% using an exact binomial test.

#### Analyses of secondary endpoints

Secondary analyses will be performed primarily on all patients (regardless of indication for neck dissection), and also in the subgroup of patients with an indication for neck dissection (as for the primary objective).

The relationship between ctDNA/cvDNA detection at 3 months post-treatment and the treatment failure rate, as well as the relapse rate during follow-up, will be evaluated using the classic diagnostic performance measures calculated on contingency tables (including PPV, NPV, sensitivity, specificity, overall accuracy). In addition, for concordance analyses (of binary variables) between ctDNA/cvDNA and primary tumour, between p16 IHS and real-time PCR, and between real-time PCR and NGS, Cohen's kappa method will also be used.

Survival will be analysed using Kaplan–Meier curves (and log-rank test if relevant). The prognostic value of the presence of residual adenomegaly will be assessed using a Cox model. Other prognostic factors for survival will be investigated using firstly univariate Cox models, and then multivariate models to assess the prognostic value of the presence of residual adenomegaly in particular, and to identify possible confounding factors. For patients with ct/cvDNA collection and analysis at 3 months after the end of treatment, the prognostic impact of ct/cvDNA detection at 3 months in particular will be analysed.

The relationship between ctDNA/cvDNA detection at diagnosis and the clinical, para-clinical and pathological characteristics of the cancer will be performed using McNemar's test, Wilcoxon's signed rank test, Spearman's correlation and multiple linear or logistic regression models, depending on the type of data.

Inter-observer reliability will be assessed using Cohen's kappa method on three-level criteria (positive, doubtful lymph node involvement, or negative).

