#### Secondary objectives and endpoints

Assessment of the cDNA detection rate among patients with residual adenomegaly after treatment. This will be evaluated according to cDNA detection and response on CT-scan.

Assessment of the relationship between cDNA detection and metabolic lymph node response on PET scan after treatment among patients with residual adenomegaly. This endpoint will be evaluated according to cDNA detection and objective metabolic response at three months after potentiated radiotherapy.

Assessment of the prognostic value of cDNA detection 3 months after the end of potentiated radiotherapy for patients with residual adenomegaly. This endpoint will be evaluated using overall survival and progression-free survival.

Assessment of the prognosis value of the presence of residual adenomegaly. This will be evaluated using overall survival and progression-free survival.

Assessment of the concordance of mutational profiles and HPV-HR genotypes between the primary tumour and cDNA at diagnosis. This endpoint will be evaluated on the basis of the mutational profiles from FFPE blocks and the inclusion blood sample.

Assessment of concordance between p16 immunohistochemistry and HPV-HR genotyping on the primary tumour.

Test of the concordance between real-time PCR and NGS on FFPE blocks for simultaneous detection and genotyping of HPV-HR at diagnosis.

Assessment of the relationship between ctDNA and cvDNA detection at diagnosis and the clinical, paraclinical and pathological features of the cancer.

Assessment of inter-observer reproducibility of the interpretation of SUVmax measures of residual cervical adenomegaly. A centralized review of the initial and three months post-treatment PET-CT will be performed by the sponsor’s nuclear medicine department.

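### M3 cDNA is scored as a diagnostic test for later relapse, mainly in pooled patients, although neck dissection intervenes in some of them and pulls the relapse PPV and specificity down

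*Protocol article*

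**What the plan says.** All references are to the protocol article.

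- **Method.** Under *Analyses of secondary endpoints*, M3 cDNA is set against two outcomes. Treatment failure comes first, and the sentence goes on: "as well as the relapse rate during follow-up, will be evaluated using the classic diagnostic performance measures calculated on contingency tables". The measures are listed as "including PPV, NPV, sensitivity, specificity, overall accuracy".
- **Population.** "Secondary analyses will be performed primarily on all patients (regardless of indication for neck dissection), and also in the subgroup of patients with an indication" (meaning one to operate on the neck). No analysis of undissected patients alone is named.
- **Survival.** *Secondary objectives and endpoints* lists "Assessment of the prognostic value of cDNA detection 3 months after the end of potentiated radiotherapy for patients with residual adenomegaly", judged on overall and progression-free survival. The analysis section uses Kaplan–Meier, log-rank and Cox methods and says that, in patients sampled at M3, "the prognostic impact of ct/cvDNA detection at 3 months in particular will be analysed". Dissection is not named as a stratum or covariate.
- **Sequence of events.** The second blood sample is taken at the three-month evaluation, only in patients with residual nodes on the scan (*Blood sample for cDNA research*). The Background says: "Cervical curage is now indicated only if the response assessed by PET-CT is only partial". Follow-up visits then run from M9 to M27 (*Study procedures and participant timeline*).
- **Primary analysis.** The reference standard is the dissection result itself, in patients who undergo dissection.

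**The concern.** Diagnostic accuracy measures assume that nothing acts on the target condition between the index test and the reference outcome. Here a salvage operation directed at that condition falls between the two, in the PET-defined part of the sampled patients and not in the rest.

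A cDNA-positive patient whose viable node is removed and who stays free of relapse is tabulated as a false positive. A cDNA-negative patient with viable disease that is removed is tabulated as a true negative. The better the surgery works, the worse the marker looks on PPV and specificity, although its ability to detect residual disease is unchanged.

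The pooled table adds a second difficulty, because it mixes patients whose neck was operated on with patients whose neck was not. The planned multivariate models do not obviously separate them. Their named focus is residual adenomegaly, which every patient sampled at M3 should have.

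**Working it through.** **1. The plan's own figures.** The article gives no figure for the relapse analyses. Its figures for the primary analysis reproduce and serve as inputs. The planned 28 patients, with half taken as cDNA-positive, give 14 positive and 14 negative. The Wilson half-length for an NPV of 89.7% with n = 14 is 16.5%, as stated. The equal split is inferred from that match; the article does not state it.

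**2. Table against the dissection result** (PPV 85%, NPV 89.7%, 14 + 14 patients):

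- True positives 14 × 0.85 = 11.9; false positives 2.1.
- True negatives 14 × 0.897 = 12.56; false negatives 1.44.
- Specificity 12.56 / (12.56 + 2.1) = 85.7%.

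**3. The same patients scored against relapse.** Let q be the share of residual-disease patients who stay relapse-free after dissection. This is an assumption; the article gives no value. Suppose first that pathology-negative patients do not relapse. Then

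- PPV = 0.85 × (1 − q)
- NPV = 1 − 0.103 × (1 − q)
- Specificity = (12.56 + 1.44q) / (12.56 + 1.44q + 2.1 + 11.9q)

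| q | PPV | NPV | Specificity | True positives scored as false | False negatives scored as true |
|---|---|---|---|---|---|
| 0 | 85.0% | 89.7% | 85.7% | 0 | 0 |
| 0.3 | 59.5% | 92.8% | 69.6% | 3.6 | 0.4 |
| 0.5 | 42.5% | 94.9% | 62.3% | 6.0 | 0.7 |
| 0.7 | 25.5% | 96.9% | 56.5% | 8.3 | 1.0 |

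The NPV effect cannot exceed the 1.44 missed patients of 28.

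**4. Adding relapse without nodal residual disease.** Assume 20% relapse in pathology-negative patients, and certain progression of viable disease that is left in place. Without dissection:

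- PPV = 0.85 + 0.15 × 0.2 = 88.0%
- NPV = 0.897 × 0.8 = 71.8%

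Now let dissection bring a share c of residual-disease patients down to the 20% level:

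- PPV = 0.85 × [(1 − c) + 0.2c] + 0.03 = 60.8%, 47.2%, 33.6% for c = 0.4, 0.6, 0.8
- NPV = 0.718 + 0.103 × 0.8c = 75.1%, 76.7%, 78.4%

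The NPV shift is 3 to 7 points, about 5 in the middle case.

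**5. Varying the background rate.** Set q = 0.5 and compare with q = 0 at the same background relapse. At 10% background, PPV goes from 86.5% to 44.0% and NPV from 80.7% to 85.9%. At 30%, PPV goes from 89.5% to 47.0% and NPV from 62.8% to 67.9%. The directions hold: a large fall in PPV and a rise of about 5 points in NPV.

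**6. What counting viable tumour as failure does.** If viable tumour in the specimen or later relapse is the event, every residual-disease patient is a failure whatever q is. PPV returns to 85% with no background relapse, or 0.85 + 0.15 × 0.2 = 88% with 20%.

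**The case against.** The strongest reply is that the plan asks how M3 cDNA relates to relapse under the care that patients receive. For that question a patient who does not relapse is correctly a non-event. Dissection is triggered by PET-CT and not by cDNA, so within the indication subgroup cDNA-positive and cDNA-negative patients are managed alike. Their comparison is a valid prognostic one, and the plan already includes that subgroup. This stands. It limits the fault to the diagnostic-accuracy framing and to the pooling.

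Two stronger readings are tempting, and the article does not support them.

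- *PFS and OS are misclassified in the same way.* They are described as prognostic value and analysed with time-to-event methods, so no patient is called a false positive or true negative there. What remains is a pooled effect over operated and unoperated patients.
- *The relapse NPV will make omitting dissection look safe.* The NPV whose precision the article plans for is the one against the dissection result, which surgery does not bias. Nothing says that the relapse NPV will be used for that purpose. The shift of about 5 points is small beside a half-length of 16.5 points.

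Two further points stand in part. The undissected sampled group may be small: the Background puts residual adenomegaly at up to 50%, and the sample size section puts the indication for dissection at about 50%. Also, treatment failure is not defined in the article. If it includes viable tumour in the specimen, that table escapes the problem, but the separately named relapse table does not.

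**Conclusion.** The point holds for the relapse tables. The article fixes both the measures and the populations, and followed as written they let successful surgery lower the marker's apparent PPV and specificity for residual disease. The size depends on how well dissection works, which the article does not give. With the plan's PPV of 85% and no other relapse, the apparent PPV is 59.5%, 42.5% or 25.5% for an assumed salvage share of 30%, 50% or 70%. At a share of zero nothing changes. The upward shift in relapse NPV is minor.

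For PFS and OS the consequence is limited to a mixed hazard ratio. The primary endpoint, its test and the sample size are not affected. This is an inexpensive improvement to a secondary analysis, not a threat to the trial's main conclusion.

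**What to change.** Amend *Analyses of secondary endpoints* as follows.

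1. Describe relapse, PFS and OS by M3 cDNA as prognostic results under care that includes dissection. Keep the terms of diagnostic accuracy for the comparison with the dissection result.
2. Report the relapse tables and survival curves separately for dissected and undissected patients sampled at M3. Stratify any pooled log-rank test or Cox model for M3 cDNA by dissection. If the undissected group is small, report it descriptively.
3. In dissected patients, add a table in which viable tumour in the specimen or later relapse counts as failure. If treatment failure already means this, say so instead.

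Dissection status and histology are needed for the primary analysis anyway, so only the analysis wording changes. The cost is small strata and wide intervals for a secondary endpoint, and possibly a nearly empty undissected stratum.

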### Participant eligibility

The exhaustive list of selection criteria is presented in Table 1. Patients with a recent diagnosis of locally-advanced head and neck cancer with lymph node involvement and never previously treated and for whom potentiated radiotherapy is indicated are eligible. After the signature of informed consent, a blood sample will be taken (2 tubes of 9 mL) and a FPPE block (from the tumour or a lymph node biopsy) will be recovered and sent to the sponsor. Centralized analyses will be conducted to identify specific tumour mutations on FFPE blocks and to search for the presence of cDNA in the blood sample. Patients for whom neither specific tumour mutations nor cDNA is found will be considered as screening failures.

**Table 1 Tab1:** Selection criteria

Inclusion criteria	Non-inclusion criteria
Age ≥ 18 and ≤ 80 years old	Tumor of the nasopharynx, sinuses, nasal cavity, salivary glands or thyroid cancer
Epidermoïd carcinoma histologically confirmed, never treated, with lymph node envolvment	Treatment with radiotherapy only
Stage III (N1), stage IVa (minimum N1) or IVb, resectable but not operated or unresectable, with potentiated radiotherapy indication	Contraindication for neck dissection
Oral cavity, oropharynx, hypopharynx or larynx, cervical adenopathies without a primitive	Metastatic disease (stage IVc)
Tumoral sample FFPE available before the treatment initiation	History of treatment for a head and neck cancer
Presence of cDNA in the initial blood sample	History of other cancer within 3 years (except carcinoma in situ, basal cell skin carcinoma, localized prostate cancer Gleason 6)
Tumor-specific variant detected on FFPE and leucocytes	Pregnant or breastfeeding woman
Written informed consent signed	Patient under guardianship or curatorship
Affiliation to the French social security system	Psychological disorder (cognitive disorders, mental alertness, etc*.*) or social (deprivation of liberty by judicial or administrative decision) or geographical reasons that may compromise medical monitoring of the trial or compliance with treatment

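### Two paired tests (McNemar, Wilcoxon signed rank) are named for an unpaired association between cDNA detection at diagnosis and cancer features

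*Protocol article*

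**What the plan says.** The protocol article, under Secondary objectives and endpoints, lists this aim: "Assessment of the relationship between ctDNA and cvDNA detection at diagnosis and the clinical, paraclinical and pathological features of the cancer".

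Under Analyses of secondary endpoints, it says this relationship "will be performed using McNemar's test, Wilcoxon's signed rank test". The same sentence goes on to "Spearman's correlation and multiple linear or logistic regression models, depending on the type of data".

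Two other statements bear on the point. Table 1 (Participant eligibility) lists as an inclusion criterion "Presence of cDNA in the initial blood sample". On numbers, Sample size calculations says "we estimate that it will be necessary to screen around 75 patients".

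**The concern.** The question is whether patients whose circulating DNA is detected at diagnosis differ in stage, site, tumour size, p16 status and the like from patients in whom it is not detected. Those are two independent groups of patients. McNemar's test and the signed rank test are built for a different situation, in which the same quantity is measured twice on the same unit or on matched units. The article describes no second time point and no matching for this objective.

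An analyst who follows the text would report p-values that do not concern the stated relationship. For a yes/no feature, McNemar's p-value depends on how common the feature is compared with detection. It can therefore be very small where no association exists, and large where a strong one does.

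**Working it through.** The article gives no sample size, power or alpha for this objective, so there is no figure of its own to reproduce. The check is by reasoning and by illustrative tables.

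**Inputs.** The total of 75 is the article's approximate number to be screened and serves only to size the tables. All cell counts are assumed, because the article gives no feature frequencies.

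**Notation.** For a yes/no feature, let a = detected with feature, b = detected without, c = not detected with feature, d = not detected without.

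**What each method tests.**
- The detection rate is (a + b)/n and the feature rate is (a + c)/n. They differ by (b − c)/n. McNemar's null hypothesis is that this difference is zero. The exact p-value is 2 × P(X ≤ min(b, c)) with X ~ Binomial(b + c, 0.5), capped at 1. The cells a and d do not enter.
- Association is measured by the odds ratio, ad/(bc), which uses all four cells. Fisher's exact test has an odds ratio of 1 as its null hypothesis.

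**Table 1: no association.** a = 24, b = 36, c = 6, d = 9.
- Detection is 60/75 = 80% and the feature rate is 30/75 = 40%.
- Odds ratio = (24 × 9)/(36 × 6) = 216/216 = 1.0. The feature is present in 24/60 = 40% of detected and 6/15 = 40% of non-detected patients.
- McNemar: 2 × P(X ≤ 6), X ~ Binomial(42, 0.5), p = 0.000003. Fisher: p = 1.00.

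**Table 2: strong association.** a = 45, b = 5, c = 5, d = 20.
- Detection and feature rates are both 50/75 = 66.7%.
- Odds ratio = (45 × 20)/(5 × 5) = 36. The feature is present in 45/50 = 90% of detected and 5/25 = 20% of non-detected patients.
- McNemar: b = c, so p = 1.00. Fisher: p = 2e-9.

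**Range over the assumed feature rate.** Keep detection at 80%, n = 75 and an odds ratio of exactly 1.0, and vary only how common the feature is:

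| Feature rate | a, b, c, d | McNemar p | Fisher p |
|---|---|---|---|
| 20% | 12, 48, 3, 12 | 2e-11 | 1.00 |
| 40% | 24, 36, 6, 9 | 0.000003 | 1.00 |
| 60% | 36, 24, 9, 6 | 0.014 | 1.00 |
| 80% | 48, 12, 12, 3 | 1.00 | 1.00 |

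The association is nil in every row. McNemar's p-value moves from 2e-11 to 1.00 only because the feature rate approaches the detection rate.

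**Signed rank test.** It ranks within-patient differences between two measurements on one scale. Here one variable is a yes/no DNA result and the other is, for example, tumour size or nodal stage. There is no meaningful difference between them to rank. Comparing the feature between detected and non-detected patients is the task of the rank-sum (Mann–Whitney) test.

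**Who can be compared.** Taking Table 1 of the article at its word, every included patient has cDNA in the initial sample, so detection of any cDNA does not vary among them. An unpaired test, and equally a logistic regression or a Spearman correlation on that variable, would then have no non-detected group. Variation remains if screened patients without cDNA are kept for this analysis, or if ctDNA and cvDNA are treated as two separate variables.

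**The case against.** The strongest reply is that the sentence does not end with the two paired tests. It also names Spearman's correlation and linear or logistic regression, chosen by type of data, and these do address association. This stands: the plan already contains a valid route to the objective, and a reader who concluded that the objective goes unanswered would go too far. But the sentence is a menu. McNemar is its only simple test for two binary variables, and chi-square, Fisher and rank-sum do not appear.

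A second reply is that test details belong in the statistical analysis plan, which is not shown. That would answer silence, but the article is not silent. It names two specific tests, and they do not fit.

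A third is that McNemar may have been meant for genuinely paired comparisons, such as p16 against PCR or PCR against NGS on the same tumour. Those have their own sentence, which assigns Cohen's kappa. The McNemar sentence concerns detection and cancer characteristics.

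A reader might also want to extend the criticism to the PET-CT reading, where the article says "Inter-observer reliability will be assessed using Cohen's kappa method on three-level criteria (positive, doubtful lymph node involvement, or negative"), and infer that the kappa is unweighted and wrong for a SUVmax objective. The documents do not support this. The article does not say whether the kappa is weighted, and weights are commonly left to the statistical analysis plan. The objective reads "Assessment of inter-observer reproducibility of the interpretation of SUVmax measures of residual cervical adenomegaly". A positive, doubtful or negative reading is an interpretation, so a three-level kappa can address it. Agreement statistics on the SUVmax value would be a preference and not a correction.

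**Conclusion.** The point holds for the two named tests. McNemar's test and the signed rank test are paired procedures assigned to an unpaired association. McNemar's would test equality of two unrelated rates, and the signed rank test has nothing to work on.

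The p-values above illustrate how McNemar's test behaves under assumed counts. They do not estimate an error rate in this trial, because the article gives no feature frequencies, and 75 is a screening number and not an analysis population for this objective.

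The consequence is limited. One secondary objective is affected, valid methods for it stand in the same sentence, and neither the primary test of positive predictive value nor the sample size depends on it. It should still be corrected, because an analysis plan that copies the sentence would carry the error forward.

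**What to change.** In Analyses of secondary endpoints, for this objective only:

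- Replace McNemar's test with the chi-square test, or Fisher's exact test where expected counts are small.
- Replace Wilcoxon's signed rank test with the Wilcoxon rank-sum (Mann–Whitney) test for continuous or ordinal features.
- Keep Spearman's correlation and the regression models as planned.
- State the analysis population: all screened patients with a baseline blood sample, including those who fail screening for lack of cDNA, or else ctDNA detection and cvDNA detection analysed as separate variables.

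The cost is wording in the protocol or the statistical analysis plan. No patients or samples are added, since the baseline blood is drawn and tested before eligibility is settled. If screening failures are used, the team needs to confirm that their baseline features are recorded and that their consent covers this use.
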